## Abstract

**Background:**

Post-operative pain of endoscopic submucosal dissection (ESD) is always be overlooked and undertreated by endoscopists. However, the incidence of moderate to severe pain after ESD is as high as 44.9% to 62.8%, which can greatly affect the patient’s recovery, reduce their satisfaction, and extend their hospital stay. Transcutaneous electrical acupoint stimulation (TEAS) have been shown to reduce postoperative pain and enhance gastrointestinal (GI) function recovery in patients undergoing abdomen surgery. However, there is no evidence regarding on the effect of TEAS on post-operative pain and complications in patients undergoing ESD. Therefore, we aim to investigate whether perioperative TEAS treatment is superior to the sham acupuncture in terms of post-ESD pain and GI function recovery.

**Methods:**

This study is a prospective, randomized controlled trail, which is single-blinded and in single center. A total of 120 patients undergoing elective gastric and esophageal ESD surgery in Beijing Friendship Hospital, Capital Medical University, will be involved in this study. These individuals will be stratified according to the type of ESD surgery (i.e. gastric or esophageal procedure) and be randomly divided into two groups. L14, PC6, ST36 and ST37 will be stimulated at the TEAS treatment group, and the control group will receive simulation at four sham acupoints. The primary outcome is post-EDS VAS score at the time of entering PACU, 10 min, 20 min, 30 min, 1 h, 2 h, 4 h, 6 h, 18 h, 24 h, 48 h after the surgery. The secondary outcomes include the anesthesia-associated parameters, sedation score, nausea and vomiting score, shivering score, recovery of gastrointestinal function, satisfaction of patients to anesthesia, incidence of postoperative complications, QLQ-C30 life quality scale, and the economic indicators.

**Discussion:**

The results of this study will confirm that continuous preventive application of TEAS can alleviate the postoperative pain among patients with gastric and esophageal ESD surgery and accelerate the recovery of post-ESD gastrointestinal function.

**Trial registration:**

Chinese Clinical Trial Registry, ID: ChiCTR2100052837, registered on November 6, 2021. http://www.chictr.org.cn/showproj.aspx?proj=135892.

**Supplementary Information:**

The online version contains supplementary material available at 10.1186/s12906-023-04075-9.

## Background

Endoscopic submucosal dissection (ESD) is a minimally invasive treatment for early gastrointestinal neoplasms, with the advantages of histological en bloc mucosal resection, accurate pathologic diagnosis, low recurrence rate, and fast recovery after surgery [1–3]. However, we should not ignore the complications after ESD. In addition to the high incidence of intraoperative bleeding and perforation, complications such as postoperative abdominal distension, abdominal pain, nausea and vomiting are also common [2, 3]. Some studies showed that the moderate to severe pain after EDS surgery can appear at the incidence of as high as 44.9–62.8%, especially in the early postoperative period (within 1-4 h after surgery) [4]. The post-ESD pain will greatly affect the patient postoperative recovery, reduce patient satisfaction, and increase length of hospital stay and medical costs [2–5]. Unfortunately, the postoperative pain after ESD is always overlooked or underestimated, partly due to the excessive engagement of earlier day of discharge and enforced early mobilization in the ERAS protocols [5, 6].

Presently, there has been no unified conclusion on how to perform effective postoperative analgesia to patients with gastric and esophageal ESD surgery. Because such patients need to be discharged quickly, overdose of opioids are often not recommended. Some studies found that intravenous dexamethasone or lidocaine, or local infusion of bupivacaine and triamcinolone during ESD procedure can help to relieve post-ESD abdominal pain, while reducing the consumption of intraoperative opioids and decreasing patient body movement [7–9]. However, it requires to be studied on how long the adjuvant analgesic effect of the above perioperative drugs can last [10]. In conclusion, the ESD patients urgently need effective postoperative analgesia methods with little impact on patient functions.

As an important part of traditional Chinese medicine, acupuncture and moxibustion are widely used to regulate organ functions during perioperative period, including the treatment of postoperative pain [11]. Transcutaneous Electrical Acupoint Stimulation (TEAS) is an improvement on traditional acupuncture. It sends electrical pulses to acupoints through electrodes on the skin surface, which is non-invasive, easily operatable, and effective for pain relief [12]. In recent years, numerous studies have demonstrated the effect of TEAS on alleviation of postoperative pain, postoperative nausea and vomiting (PONV), enhancement of gastrointestinal function recovery, and reduction of stress reaction [11–13].

In our previous study, it was found that preventive continuous application of TEAS can reduce postoperative pain and promote gastrointestinal function recovery in patients undergoing laparoscopic resection of gastroesophageal tumors [14–16]. However, if TEAS have the same effect on postoperative pain of minimally invasive surgery such as ESD is remained unexplored. Therefore, this study tries to demonstrate that preventive applying TEAS to superior acupoints can reduce postoperative pain and promote the recovery of gastrointestinal function in patients undergoing gastroesophageal ESD surgery.

## Methods and design

This trial has been approved by the Ethics Committee of Beijing Friendship Hospital, Capital Medical University (Approval No: 2021-P2-315-01), and has been registered in the Clinical Trial Registry (Chictr) with number: ChiCTR2100052837 (see Additional file 1). The study will be implemented at Beijing Friendship Hospital and will be carried out in accordance with the principles of the Declaration of Helsinki (version Edinburgh 2000). Additional file 2 shows the SPIRIT 2013 Checklist, which this protocol is based on.

### Aim

This trail aims to confirm that the preventive application of TEAS in patients undergoing gastroesophageal ESD surgery can release postoperative pain while promoting recovery of gastrointestinal function. Moreover, we can provide clinical evidence for the inclusion of perioperative TEAS into enhanced recovery after surgery (ERAS) of gastrointestinal surgery.

### Trial design

This study is a single-center, prospective, single-blind, randomized, and controlled trial. A total of 120 patients undergoing elective gastric and esophageal ESD surgery in Beijing Friendship Hospital, Capital Medical University, will be stratified by the type of ESD surgery (i.e. gastric or esophageal procedure) at 1:1 ratio and be randomized into two groups: the sham group (Group S, *n* = 60) and the TEAS treatment group (Group T, *n* = 60). Each group has 30 gastric cases and 30 esophageal cases (Fig. 1). The observers will conduct screening according to the pre-standard plan. Data gathering will start from the collection of basic data and last until the end of follow-up (Table 1). According to the hospital regulations, compensation and post-trial care will be provided to those injured due to their participation in the trial.

**Fig. 1 Fig1:**
[figure not shown]
Consolidated Standards of Reporting Trials (CONSORT) diagram for this trail

**Table 1 Tab1:**
[figure not shown]
Standard Protocol Items: Recommendations for Interventional Trials (SPIRIT) Schedule for enrollment, interventions, and assessments

### Randomization and blinding

This is a single-blinded study. To minimize evaluation bias, the evaluators responsible for screening and outcome evaluation will be blinded to the grouping information. The anesthesiologist, and the acupuncturist who is in charge of the TEAS stimulation from the traditional Chinese department, will acknowledge each patient’s affiliation, but will be isolated to the research results. Patients will not be informed about their group assignment. Randomization will be performed by a computer-generated blocked randomization order. A nurse will generate the allocation sequence and prepare the sealed, numbered envelops. Each envelop will be unfolded by the anesthesiologist until the patient entering the operating room. Subjects will be randomly assigned to the sham group or the TEAS group with a ratio of 1:1 by the anesthesiologist according to these envelops. The case report forms (CRF) will be used to record all the original data needed.

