### Standard procedures

The following approaches are suggested (Fig. 2):

The anesthesiologist will perform preoperative education on patients who meet the inclusion criteria and make sure they can understand and utilize VAS and NRS to evaluate their degree of pain and nausea when patients are admitted into operation room. Explaining to patients of the research purpose, process, risks and benefits, and other related contents. Guaranteeing that they are willing to adhere to trail schedule. Finally, ensuring that self-reported information sheet which is used in postoperative follow-up is issued and the informed consent is signed.Electrocardiogram, blood pressure, pulse oxygen saturation and BIS will be performed.The TEAS or sham stimulation will be conducted by the experienced anesthesiologist and acupuncturist at 30 min before the surgery until the end of the operation.Rapid sequence induction is applied as anesthesia induction strategy. Midazolam 0.03 mg/kg, remifentanil 1-2 μg/kg, etomidate 0.1–0.2 mg/kg and rocuronium 0.6–0.8 mg/kg is used before intubation. When the patients lose their consciousness, mask ventilation is given. Mechanical ventilation will be performed after endotracheal intubation (tube size 7.5 for male and 7.0 for female).Anesthesia is maintained with total intravenous infusion of propofol (4-6 mg/kg/h), remifentanil (0.05–0.2 µg/kg/min) and rocuronium (one third of the induced dose every 40 min). Anesthetic depth is controlled by the adjustment of infusion speed of intravenous propofol to maintain a bispectral index at 45–55 during procedure. The analgesia nociception index (ANI) is maintained at 50–70 by regulating the speed of remifentanil intravenous infusion. Respiratory parameters are adjusted to maintain PetCO_2_ at 35–45 mmHg. The infusion of sedative and analgesic agents are stopped after suture of the operative incision.Under the premise of maintaining appropriate anesthesia depth, atropine 0.25–0.5 mg at one time is given if heart rate (HR) is under 50 times per minute and esmolol 0.2–0.5 mg/kg is administrated if HR is above 100 times per minute. If the mean blood pressure is below 65 mmHg or decrease by more than 20% of baseline, ephedrine 6 mg will be given. Tramadol 50 mg is applied for analgesia 30 min before the end of ESD surgery.At the end of surgery, patients will be extubated and transferred to the postoperative care unit (PACU) in routine.The Visual Analogue Scale (VAS) will be utilized to evaluate the extent of the pain of patients, and if VAS score ≥ 4 points or the patients asked for analgesia during the follow-up period, morphine 1 mg will be administered intravenously. The Numerical Rating Scale (NRS) is used to evaluate the degree of nausea. If NRS ≥ 7 or vomiting occurs, serotonin 3 receptor antagonist will be given. Concomitant medication administration during the trial period from the beginning of surgery to 2 days after the end will be recorded.

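### The unblinded anesthesiologist role that opens the envelopes of a blocked, stratified sequence also teaches the pain scale and secures consent, so the next arm can be predicted better than chance before those steps are finished

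*Protocol article*

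**What the plan says.** Under Randomization and blinding, the article states that "Randomization will be performed by a computer-generated blocked randomization order". Preparation is separated from use: "A nurse will generate the allocation sequence and prepare the sealed, numbered envelops". The anesthesiologist then opens them: "Each envelop will be unfolded by the anesthesiologist until the patient entering the operating room". The word "until" leaves the exact moment unclear, but the opening is tied to entry to the operating room. The same role makes the assignment ("Subjects will be randomly assigned to the sham group or the TEAS group with a ratio of 1:1 by the anesthesiologist") and is unblinded: "The anesthesiologist, and the acupuncturist who is in charge of the TEAS stimulation from the traditional Chinese department, will acknowledge each patient’s affiliation". That section also says that the evaluators who screen patients and assess outcomes are blinded.

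Trial design adds that patients "will be stratified by the type of ESD surgery (i.e. gastric or esophageal procedure) at 1:1 ratio", and that "Each group has 30 gastric cases and 30 esophageal cases".

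The first step of Standard procedures reads: "The anesthesiologist will perform preoperative education on patients who meet the inclusion criteria". It covers making sure that patients can use the VAS and NRS, explaining purpose, risks and benefits, and seeing that consent is signed. It is placed at admission to the operating room. A later step has the anesthesiologist and the acupuncturist deliver TEAS or sham.

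The exclusion criteria include inability to understand the two scales and an open criterion of unsuitability. The article does not say who judges the latter. The primary outcome is the patient's own VAS rating.

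**The concern.** Sealed envelopes conceal a single assignment. They do not hide the history of assignments from the person who opens them. When the sequence is forced into balance, that history carries information about the next envelope. Here one role holds the history and also completes the last steps before a patient is in the trial.

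The risk is that a guess about the coming arm, even an unconscious one, colors how trial entry is presented, how strictly understanding of the scales is judged, or how the VAS is explained. The last matters because patients rate the primary outcome themselves. The patient's blinding does not protect against this, because the influence would come before treatment starts.

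Settling eligibility and consent before the envelope is opened would not remove the problem if the same role still performed them, because the prediction uses earlier patients' arms and not the sealed one.

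**Working it through.** **Inputs**
- 30 gastric and 30 esophageal cases per arm (Trial design).
- Blocked sequence, ratio 1:1 (Randomization and blinding).
- Block size: not stated, so a range is shown. The sizes used all divide 60.
- Assumptions: one list per procedure type, which is the natural reading of stratification though not spelled out; and a guesser who has seen, or been told, all earlier arms in the stratum.

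**The plan's own totals.** 2 arms × 2 procedure types × 30 = 120, or 60 per arm. Each stratum is a list of 60 split 30/30. The figures agree.

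**Why block size need not be known in order to guess.** Every completed block is balanced and adds nothing to the difference between arms. The running difference in a stratum is therefore the imbalance inside the current block. Guessing the arm that is behind, or either arm when tied, needs only a count of past arms.

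**Correct guesses.** For a block of size 2n, the expected number of correct guesses is n + 2^(2n−1)/C(2n,n) − 1/2.
- Block of 4 (n = 2): 2 + 8/6 − 0.5 = 2.833, and 2.833/4 = 70.8%. By hand, the four positions give 1/2 + 2/3 + 2/3 + 1 = 2.833.
- Block of 6 (n = 3): 3 + 32/20 − 0.5 = 4.1, and 4.1/6 = 68.3%.
- Block of 10 (n = 5): 5 + 512/252 − 0.5 = 6.53, and 6.53/10 = 65.3%.
- One block of 60 (n = 30), which represents the 30/30 total with no smaller blocks: 34.37/60 = 57.3%.

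**Assignments known with certainty.** The expected share is 1/(n + 1). Unlike the guess rate, this requires knowing where a block ends.

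| Block size | Correct guesses | Certain, if block size is known | Certain, of 120 |
|---|---|---|---|
| 4 | 70.8% | 33.3% | 40 |
| 6 | 68.3% | 25.0% | 30 |
| 10 | 65.3% | 16.7% | 20 |
| 20 | 61.7% | 9.1% | 11 |
| 60 | 57.3% | 3.2% | 4 |
| Unrestricted | 50% | 0% | 0 |

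Only the row for 60 rests on a total that the article states. The rows above it show what smaller blocks would add.

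**Where a guess could act.** Screening is done by blinded evaluators, and the anesthesiologist's education step concerns patients who already meet the inclusion criteria. That leaves three points in that step: the talk leading to consent, the check of scale understanding (failure is an exclusion), and the teaching of the VAS.

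**The case against.** The strongest case on the other side has four parts.

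- **Blinded screening.** Evaluators who do not know the allocations screen patients, and the anesthesiologist acts afterwards. This stands and narrows the route considerably. A reader might infer that trial entry is effectively unconcealed, but the article does not support that. Nor does it say that the anesthesiologist decides who is unsuitable.
- **A role is not a person.** Nothing says that one anesthesiologist handles successive patients over roughly two years of recruitment. Several who did not share a count would predict less well. This stands, so the point is conditional on continuity or a shared tally.
- **Undisclosed block size.** Not publishing block size is normal and is not criticized here. Blocks may be large or vary. The objection stands for the upper part of the range and for every certain share above that for one block of 60. It does not bring the guess rate down to 50%, because forced balance makes the running count informative whatever the block size. The 30/30 statement could also be read as a target; the sequence would still be blocked.
- **No evidence of harm.** A reader might infer an inflated false-positive rate of a definite size. Such a figure needs an assumed difference in VAS between patients entered under one guess and the other. The document gives no basis for choosing that difference, so none is offered.

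**Conclusion.** The weakness is real but limited. One unblinded role opens the envelopes, treats the patients, teaches the scales and secures consent, under a sequence whose history predicts its next entry better than chance. The correct-guess rate is about 57% from the 30/30 total alone and up to about 71% with blocks as small as 4, against 50% for an unpredictable sequence. The range assumes separate lists per procedure type and an anesthesiologist who sees or shares past arms.

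A reader might infer that the next arm is often known outright. That would need a known, small block size. On the 30/30 total alone, about 4 of 120 assignments are certain, all near the end of a stratum. The document shows neither that anyone has steered entry nor how much bias steering would cause. The case for change is that the exposure is avoidable at little cost.

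**What to change.** Amend the first step of Standard procedures so that the blinded screening evaluator already named under Randomization and blinding, and not the role that opens the envelopes, completes the VAS/NRS check, the trial education and the consent. State that all of this is finished and recorded before that patient's envelope is opened. This also settles the unclear order of events around entry to the operating room.

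The randomization sequence can stay as it is. The change applies to patients still to be recruited: with 70 of 120 included when the article was written, that was 120 − 70 = 50.

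The cost is a small shift of tasks between existing staff and an amended step. No extra patients or new roles are needed. The evaluator must not be told past allocations, which the blinding section already requires.

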### Study participants and recruitment

We will recruit 120 patients who are scheduled to undergo gastric or esophageal ESD procedure. These participants will be recruited from Beijing Friendship Hospital affiliated to Capital Medical University after they are up to the eligibility criteria and sign the informed consent. We enrolled the first patient on December 1st, 2021, and will end up recruiting on December 30th, 2023. Full communication and some small gifts such as keychains will be provided for patients to encourage the enrollment. All subjects will sign the informed consent form to participate in this clinical trial, allowing the researchers to collect and analyze their data.

***Inclusion criteria include the following:***

Aged 18–75 years, diagnosed at gastric or esophageal tumor undergoing ESD procedure, regardless of gender.18 kg/m^2 ^≤ BMI ≤ 30 kg/m^2^ [body mass index = weight (kg)/height (m)^2^].American Society of Anesthesiologists (ASA) classification levels I–III.Participating in the study voluntarily and signing informed consent.

***Exclusion criteria include the following:***

Surgical incision or scar in the meridian of the acupoints of Hegu (L14), Neiguan (PC6), Shangjuxu (ST37), Zusanli (ST36).Local skin infection at the acupoints above.Upper limb or lower limb nerve damage.Participating in other clinical studies within the past 4 weeks.Inability to understand the numeric rating scale (NRS) score and the visual analog scale (VAS) score.Application to a pacemaker.Gravida, puerperant and patients with positive urine pregnancy tests.Combined with preoperative pain, using central analgesic drugs, addicted to or dependent on opioids.Preoperative complications including severe CNS diseases or severe mental diseases.Considered not suitable for this study.

***Discharge criteria are as follows:***

Requirement for participants to withdraw during the trail.Rejection of administration of remedy medication after surgery.Violation of the test program.Arising of serious adverse events (AEs).Transferred to open surgery.The duration of ESD procedure > 4 h.

### Standard procedures

The following approaches are suggested (Fig. 2):

The anesthesiologist will perform preoperative education on patients who meet the inclusion criteria and make sure they can understand and utilize VAS and NRS to evaluate their degree of pain and nausea when patients are admitted into operation room. Explaining to patients of the research purpose, process, risks and benefits, and other related contents. Guaranteeing that they are willing to adhere to trail schedule. Finally, ensuring that self-reported information sheet which is used in postoperative follow-up is issued and the informed consent is signed.Electrocardiogram, blood pressure, pulse oxygen saturation and BIS will be performed.The TEAS or sham stimulation will be conducted by the experienced anesthesiologist and acupuncturist at 30 min before the surgery until the end of the operation.Rapid sequence induction is applied as anesthesia induction strategy. Midazolam 0.03 mg/kg, remifentanil 1-2 μg/kg, etomidate 0.1–0.2 mg/kg and rocuronium 0.6–0.8 mg/kg is used before intubation. When the patients lose their consciousness, mask ventilation is given. Mechanical ventilation will be performed after endotracheal intubation (tube size 7.5 for male and 7.0 for female).Anesthesia is maintained with total intravenous infusion of propofol (4-6 mg/kg/h), remifentanil (0.05–0.2 µg/kg/min) and rocuronium (one third of the induced dose every 40 min). Anesthetic depth is controlled by the adjustment of infusion speed of intravenous propofol to maintain a bispectral index at 45–55 during procedure. The analgesia nociception index (ANI) is maintained at 50–70 by regulating the speed of remifentanil intravenous infusion. Respiratory parameters are adjusted to maintain PetCO_2_ at 35–45 mmHg. The infusion of sedative and analgesic agents are stopped after suture of the operative incision.Under the premise of maintaining appropriate anesthesia depth, atropine 0.25–0.5 mg at one time is given if heart rate (HR) is under 50 times per minute and esmolol 0.2–0.5 mg/kg is administrated if HR is above 100 times per minute. If the mean blood pressure is below 65 mmHg or decrease by more than 20% of baseline, ephedrine 6 mg will be given. Tramadol 50 mg is applied for analgesia 30 min before the end of ESD surgery.At the end of surgery, patients will be extubated and transferred to the postoperative care unit (PACU) in routine.The Visual Analogue Scale (VAS) will be utilized to evaluate the extent of the pain of patients, and if VAS score ≥ 4 points or the patients asked for analgesia during the follow-up period, morphine 1 mg will be administered intravenously. The Numerical Rating Scale (NRS) is used to evaluate the degree of nausea. If NRS ≥ 7 or vomiting occurs, serotonin 3 receptor antagonist will be given. Concomitant medication administration during the trial period from the beginning of surgery to 2 days after the end will be recorded.
